## Abstract

**Background:**

Prostate cancer is the most common male cancer in developed countries and diagnosis and treatment carries with it substantial morbidity and related unmet supportive care needs. These difficulties may be amplified by physical inactivity and obesity. We propose to apply a multimodal intervention approach that targets both unmet supportive care needs and physical activity.

**Methods/design:**

A two arm randomised controlled trial will compare usual care to a multimodal supportive care intervention "Living with Prostate Cancer" that will combine self-management with tele-based group peer support. A series of previously validated and reliable self-report measures will be administered to men at four time points: baseline/recruitment (when men are approximately 3-6 months post-diagnosis) and at 3, 6, and 12 months after recruitment and intervention commencement. Social constraints, social support, self-efficacy, group cohesion and therapeutic alliance will be included as potential moderators/mediators of intervention effect. Primary outcomes are unmet supportive care needs and physical activity levels. Secondary outcomes are domain-specific and health-related quality of life (QoL); psychological distress; benefit finding; body mass index and waist circumference. Disease variables (e.g. cancer grade, stage) will be assessed through medical and cancer registry records. An economic evaluation will be conducted alongside the randomised trial.

**Discussion:**

This study will address a critical but as yet unanswered research question: to identify a population-based way to reduce unmet supportive care needs; promote regular physical activity; and improve disease-specific and health-related QoL for prostate cancer survivors. The study will also determine the cost-effectiveness of the intervention.

**Trial Registration:**

ACTRN12611000392965

## Background

Prostate cancer is the most common male cancer in developed countries (excluding non-melanoma skin cancer) [1]. In 2004 nearly 100,000 Australian men were living with a diagnosis [2]; and in Australian men aged 60 years and over, prostate cancer accounted for 4.9% of total disability-adjusted life years (DALYs) and 17.8% of cancer-related DALYs as at 2003 [3]. With increasing incidence and 10-year survival currently around 77% [2] the large cohort of men in our community living with the sequelae of diagnosis is increasing. Therefore, the well-being of men with prostate cancer is of high public health significance.

Side effects of treatment for prostate cancer include urinary incontinence, bowel and erectile dysfunction [4]. In a recent longitudinal study assessing 1649 men diagnosed with prostate cancer three years previously, relative to a healthy aged matched population, each of the main treatments led to persistent negative effects on disease-specific quality of life (QoL) [5]. Across all treatments 36% to 87% of men reported erectile dysfunction; after radical prostatectomy 12% of men had persistent urinary incontinence; and 15% of men who had external beam radiotherapy had moderate/severe bowel problems. Unmet supportive care needs are highly prevalent in men with prostate cancer: more than half (54%) of men with prostate cancer express some level of unmet psychological need and 47% express unmet sexuality needs [6]. Three of the 10 most frequently reported unmet needs relate to sexuality, three to psychological concerns, and two each in the physical/daily living and health system and information domains. Need was greatest in those with poor health; the gradients in odds ratios of unmet need were up to five-fold between best and poorest health groups. Hence there is a link between overall health and unmet supportive care needs.

Relevant to this, most men diagnosed in Australia are over 55 years of age; many experience co-morbid chronic illness such as cardiovascular disease; and many are overweight and sedentary. There is emerging evidence that obesity is related to a higher risk of biochemical recurrence and prostate-cancer specific death for men with prostate cancer [7,8]. Higher levels of physical activity and muscle strength may enhance men's ability to regain and manage urinary and bowel symptoms and improve erectile function. A cross-sectional study [9] reported that for men who received external beam radiation therapy within the past 18 months, levels of physical activity were positively associated with sexual functioning. Wolin (2009) [10] found lower incontinence in prostate cancer survivors who were normal weight and physically active compared to survivors who were obese and sedentary. They also reported that after 58 weeks post-surgery the incidence of incontinence was the same for overweight but physically active men compared to normal weight but sedentary men. Thus, interventions seeking to make a significant impact on the well-being of men who have been previously treated for prostate cancer should assess the potential for physical activity to improve outcomes.

To date no intervention research specifically targeting unmet supportive care needs after prostate cancer has been reported [11]. As well, only a few prospective exercise studies have been conducted with prostate cancer survivors [12-16], and none of these examined unmet supportive care needs. Accordingly, in this trial we apply a multimodal intervention approach that targets both unmet supportive care needs *and *physical activity. We do this by using two main strategies: self-management and group peer support. Self-management interventions have shown consistent positive effects across a range of chronic illnesses and have great potential as a cost effective method of providing support to people affected by cancer; and address issues of equity, accessibility and choice. In addition, we uniquely trial the ability of remotely-delivered, tele-based group peer support to enhance the effectiveness of self-management for men with prostate cancer. Peer support has relatively high uptake amongst men with prostate cancer with men reporting that peer discussions provide information, emotional support, and reduce feelings of social isolation [17]. We propose that adding group peer support to self-management will have increased efficacy through the mechanisms of social support; cognitive processing; lessening of stigma; and peer-based modelling of adaptive coping.

## Methods/Design

### Study Aims and Hypotheses

The overall study aim is to compare usual care to a multimodal supportive care intervention "Living with Prostate Cancer" that will combine self-management with tele-based group peer support. In doing so we will also compare the cost-effectiveness of the support intervention relative to usual care; and identify demographic, medical and psychosocial variables that predict improvement in adjustment in prostate cancer patients with the intervention approach. The study has two arms: 1) usual care; and 2) multimodal supportive care - self-management plus six months of monthly tele-based group peer support.

It is hypothesised that 3, 6 and 12 months after recruitment and commencement of the intervention:

1. Relative to men who receive usual care, men who receive the multimodal supportive care intervention will have: fewer unmet supportive care needs; greater improvements in quantity and quality of physical activity.

2. Intervention-driven improvements in unmet supportive care needs and physical activity will be mediated by self-efficacy and moderated by social constraints and social support.

3. For all men, those who show the greatest improvements over time in physical activity will also have the greatest improvements in unmet supportive needs; disease-specific and health-related QoL.

4. The multimodal supportive care intervention will be more cost-effective compared to usual care.

### Intervention

Usual care will consist of the man's standard medical management and a package containing existing evidence-based patient education materials. The multimodal supportive care intervention "Living with Prostate Cancer" will include self-management and tele-based group peer support. All men in the multimodal intervention condition will receive a printed feedback sheet with baseline assessments of unmet need, their distress thermometer score, body mass index, waist circumference and physical activity levels. This will assist them to identify potential target areas for improvement; evaluate prime concerns; and set self-management goals. As well, a password protected website will be developed utilising Web 2.0 technology to guide men through program materials and other relevant existing web-based resources in an interactive online environment. This will allow each man to access other topic areas should his needs change; locate misplaced resources; access other helpful resources; and interact with other men in the study.

The exercise module of the intervention will focus on low cost strategies that are easily implemented in any geographic area. Participants will be encouraged to meet the physical activity targets recommended for cancer survivors [18-20]. Each participant will be provided with an elastic exercise device (Gymstick, Finland) and a watch with heart rate monitor (Polar, Finland) so that all men have the basic equipment to pursue an effective exercise program even in rural or remote settings with no additional facilities.

The tele-based group peer support will be conducted through teleconference and will be co-facilitated by a nurse counsellor and experienced trained peer. A peer is a man who has been previously diagnosed with prostate cancer and who is physically and emotionally well enough to provide support to others. The focus of the peer support groups will be on sharing experiences to facilitate peer learning, coping self-efficacy, emotional/social support and processing of experiences. The groups will have up to eight members and will be formed as men are recruited. Groups will run for six months with monthly teleconferenced meetings.

### Participants

With the strong endorsement and support of Queensland Urologists, recruitment will be undertaken through the Queensland Cancer Registry (QCR), a population-based register of cancer diagnoses in Queensland. Clinicians will be approached for permission to contact their patient about the study. Where the doctor has given permission for contact, those patients will be contacted for consent to be in the study [21,22]. Informed written consent will be obtained before study commencement and data collection. Figure 1 illustrates the recruitment, intervention and data collection process.

**Figure 1 F1:**
[figure not shown]
**Flowchart of recruitment, intervention and assessment**.

Inclusion criteria are that the men must: (1) have recently been diagnosed with localised prostate cancer (men will be three to six months post-diagnosis at recruitment); (2) be able to read and speak English; (3) have no previous history of head injury, dementia or psychiatric illness; (4) have no other concurrent cancer; (5) have phone access; and (6) have physician clearance to participate in the study. The diagnosing clinician will assist in determining eligibility as part of the consent process through the QCR.

Approximately 590 men will be recruited to the study (allowing 15% attrition from treatment; 250 men in each condition will complete final assessments). According to a Monte Carlo simulation run through Mplus, this sample size will provide between 80-85% power to detect standardised intervention effect sizes of .5 (moderate) for the dichotomous outcomes even with completion rates of 70% that are lower than the projected 85%. Power for the continuous outcomes is naturally higher for the same sample sizes, as evidenced by simulations by Jo and colleagues [23].

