## Discussion

This study will develop and evaluate a novel population-based intervention to reduce unmet supportive care needs; promote regular physical activity; and improve disease-specific and health-related QoL for prostate cancer survivors. To our knowledge, to date no supportive care intervention studies have targeted unmet supportive care needs for men with prostate cancer; trialled peer support as a method of enhancing self-management in this setting; or been adequately powered and designed to look differentially at individual differences [11]. This research will overcome these limitations, plus evaluate the cost-effectiveness of such an intervention. The intervention will be able to be utilised in a range of settings including broad reach tele-health support programs; health websites; and through support services and support groups internationally. This means that project outputs will be immediately translatable into practice to improve the overall well being of men with prostate cancer.

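### The Discussion presents the trial as adequately powered for individual differences, but the only stated power is for the main intervention effect and implies low power for moderation of dichotomous outcomes

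*Protocol article*

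**What the plan says.** **Sample size and power (Methods/Design, Participants).** "Approximately 590 men will be recruited to the study", "allowing 15% attrition from treatment; 250 men in each condition will complete final assessments". From a Monte Carlo simulation in Mplus, "this sample size will provide between 80-85% power to detect standardised intervention effect sizes of .5 (moderate) for the dichotomous outcomes", and this is said to hold "even with completion rates of 70% that are lower than the projected 85" per cent. Continuous outcomes are said to have more power, without a figure.

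**Hypotheses (Study Aims and Hypotheses).** Hypothesis 2 expects the intervention's effects on both primary outcomes to be moderated by social constraints and social support, and mediated by self-efficacy. The aims also include finding which characteristics predict who improves with the intervention.

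**Claim (Discussion).** Earlier supportive care studies are said not to have "been adequately powered and designed to look differentially at individual differences". The next sentence is "This research will overcome these limitations", followed by the cost-effectiveness aim.

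The article gives no power figure for any moderation analysis.

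**The concern.** Moderation is tested by an interaction: the difference between the intervention effect in one kind of man and in another. Such a difference is estimated much less precisely than the overall effect, so a sample sized for the overall effect is usually too small for an interaction of similar size. The only power shown is for the overall effect, and it sits at the conventional 80-85%, with little to spare.

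What is at stake is how the Hypothesis 2 results will be read. If the trial is described as adequately powered for individual differences, a non-significant interaction invites the conclusion that the intervention works equally well whatever a man's social support or constraints. The design may not be able to bear that conclusion.

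**Working it through.** **Inputs.** From Participants: 590 recruited, 85% projected completion, 70% pessimistic completion, 80-85% power for an effect of .5 on dichotomous outcomes. From Study Integrity: 1:1 allocation. Assumed, because not stated: two-sided 5% test (critical value 1.960) and a moderator that splits the men 50:50.

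**Step 1. Headcount.** 590 × 0.85 = 501.5, or about 250 per arm, which reproduces the stated figure. 590 × 0.70 = 413, or about 206 per arm.

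**Step 2. What 80-85% power says about the main effect.** Power ≈ Φ(δ − 1.960), where δ is the effect divided by its standard error (SE).
- 80%: δ = 1.960 + 0.842 = 2.802
- 85%: δ = 1.960 + 1.036 = 2.996

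This holds whatever model was simulated, because it starts from the power and not from the effect scale.

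**Step 3. SE of an interaction.** Each half of a 50:50 split holds half the men, so the effect within a half has twice the variance of the overall effect. The difference between two such effects has four times that variance, so its SE is twice the main-effect SE. For a dichotomous outcome this is approximate and assumes similar event rates in the two halves.

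**Step 4. Power for an interaction at 70% completion.**
- Same size as the main effect: Φ(2.802/2 − 1.960) = Φ(−0.559) = 29%; Φ(2.996/2 − 1.960) = Φ(−0.462) = 32%
- Half that size: Φ(2.802/4 − 1.960) = 10%; Φ(2.996/4 − 1.960) = 11%

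**Step 5. At 85% completion.** δ grows by √(0.85/0.70) = 1.102, to 3.087 and 3.301.
- Same size: Φ(3.087/2 − 1.960) = 34%; Φ(3.301/2 − 1.960) = 38%
- Half that size: Φ(3.087/4 − 1.960) = 12%; Φ(3.301/4 − 1.960) = 13%

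**Step 6. Continuous outcome, single time point, computed directly.** Interaction SE = 2√(2/n) in SD units, n per arm.

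| Completers per arm | SE | .5 SD interaction | .25 SD interaction |
|---|---|---|---|
| 206 | 0.197 | Φ(2.537 − 1.960) = 72% | Φ(1.269 − 1.960) = 24% |
| 250 | 0.179 | Φ(2.795 − 1.960) = 80% | Φ(1.398 − 1.960) = 29% |

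For scale: if the average effect were .5, an interaction of .5 would mean effects of .75 in one half and .25 in the other, a threefold difference. An interaction of .25 would mean .625 and .375.

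**The case against.** **The Discussion sentence is general.** It contrasts this trial with earlier literature, joins power with design, and states no power for any interaction. A separate moderation calculation may also exist in a fuller document. This is fair, and the absence of a calculation is not the point. The point is that the article claims the limitation is overcome, and the one figure it prints does not bear that out.

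**A reader might infer that the 80-85% contradicts the claim.** It does not. The figure concerns the intervention effect on dichotomous outcomes and is silent on moderation. For continuous outcomes a .5 SD interaction reaches 72-80% before any gain from repeated measures. The claim is unsupported, not contradicted.

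**A reader might also infer that the 80-85% is itself wrong.** At 206 per arm, with control rates of 47-54%, ordinary readings of a standardised .5 give about 98-99.9%. But those rates come from the Background ("more than half (54%) of men with prostate cancer express some level of unmet psychological need and 47% express unmet sexuality needs") and are not stated as power inputs. The simulation's event rate, effect scale, significance level and model are not given, and some readings do reach the figure. A probit shift of .5 diluted to .35 by 70% uptake gives 80-81% at 206 per arm. Control rates of 16-18% give 81-85%. So no error is shown.

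**If true main-effect power is higher, so is interaction power.** This stands. With main-effect power of about 99.5%, δ = 1.960 + 2.576 = 4.536. An equal-sized interaction then has Φ(4.536/2 − 1.960) = 62% power, and one half that size Φ(4.536/4 − 1.960) = 20%. Even this generous reading does not reach 80%.

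**The moderators are scale scores, not a split.** Also true, but the benchmark carries over. For a standardised continuous moderator, the slope within an arm has variance σ²/n, so the difference in slopes has variance 2σ²/n, the same as the main effect. The contrast between men one SD above and one SD below the mean is twice that difference, so its SE is again twice the main-effect SE.

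**Conclusion.** The point holds in a limited form. On the article's own 80-85%, moderation of a dichotomous outcome has about 29-32% power for an interaction as large as the main effect at 70% completion, 34-38% at 85%, and about 10-13% for one half that size. On a continuous outcome, only a .5 SD interaction comes near conventional power (72-80%); a .25 SD interaction has 24-29%.

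These figures assume a two-sided 5% test and a balanced moderator. The continuous-outcome figures also assume a single time point, so repeated measures would raise them by an amount the article does not allow one to compute. The dichotomous figures take the stated power at face value.

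The claim of adequate power for individual differences is therefore not supported by the stated design, particularly for dichotomous outcomes. The documents do not support going further, to say that the sample size statement is miscalculated or that the two passages contradict each other. Hypothesis 3, which concerns associations across all men, is not an interaction with treatment and is not touched by this calculation.

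**What to change.** 1. In the Discussion, delete the implication that the trial overcomes a lack of power for individual differences, or qualify it. For example: *The trial is sized for the overall intervention effect; analyses of moderation are exploratory.*
2. Report the Hypothesis 2 moderation analyses as exploratory, giving each interaction estimate with its confidence interval. State that a non-significant interaction will not be taken as evidence of no moderation.
3. As a clarification only, name the effect scale and the control rate beside the 80-85% figure.

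The cost is wording. The sample size, measures and analysis models stay as they are. The one real downside is that the trial's claim about moderation becomes less favourable.

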### Study Integrity

Ethical approval has been obtained from the Griffith University Human Research Ethics Committee (Approval: PSY/F6/10/HREC). The study design will be guided by the CONSORT criteria [24]. Randomisation to study condition will occur following the completion of baseline assessment. Assessments will be by telephone and self-report written questionnaires and project staff tracking assessments will be blinded to condition where possible. Randomisation will occur in blocks of 16, with each condition randomly generated 8 times within each block to ensure an unpredictable allocation sequence with equal numbers of men in each condition at the completion of each block; and sufficient men to form a tele-based group (of 6-8) in the multimodal supportive care condition. This sequence will be undertaken by the project manager and concealed from investigators. The group sessions will be audiotaped with 25% reviewed to ensure adherence to a peer support approach. Analyses will be conducted on the basis of intention to treat.

### Measures

A series of previously validated and reliable self-report measures will be administered to men at four time points: baseline/recruitment (when men are approximately 3-6 months post-diagnosis) and at 3, 6, and 12 months after recruitment and intervention commencement. Baseline assessments will be conducted by telephone to facilitate completion of assessments prior to randomisation. Follow-up assessments will be conducted through written questionnaires that will be mailed to participants. Social constraints, social support, self-efficacy, group cohesion and therapeutic alliance will be included as potential moderators/mediators of intervention effect. Primary outcomes are unmet supportive care needs and physical activity levels. Secondary outcomes are domain-specific and health-related QoL; psychological distress; benefit finding; body mass index and waist circumference (the following list describes the measures in detail). Disease variables (e.g. cancer Gleason score, stage) will be assessed through medical and cancer registry records.

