##### Physical Activity

All men will complete the Godin Leisure-Time Exercise Questionnaire [33]. This questionnaire assesses the average frequency of mild, moderate and strenuous exercise during free time in a typical week. Motivational readiness for physical activity will be assessed with a four item scale that asks about current levels of physical activity and intention to become more physically active [34]. In addition, men in the intervention arm only will complete simple activity diaries assessing mode, duration and intensity of physical activity entering data from the heart rate watches provided for a seven day period at the baseline assessment before the intervention commences.

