### Statistical Analyses

This study is a multivariate, two-condition randomised controlled trial with repeated measures across time and continuous and dichotomous outcome variables. The analysis of longitudinal differences in outcome will use two complementary statistical approaches: multilevel (mixed) modelling (MLM) and growth mixture modelling (GMM) as applied to randomised preventative interventions by Muthén [47]. These procedures allow the testing of typical group level predictions such as Hypothesis 1 that men in the intervention condition will have better outcomes than the usual care group. However, by incorporating the hierarchical structure of assessment points nested within individual men they further permit the true assessment of individual change in unmet needs and of the individual predictors of such change (Hypotheses 2 and 3). Consequently (and unlike traditional approaches), such models deal with the heterogeneity of responses, such as that expected in the outcomes of the proposed study, by including such variation as an explicit model term. MLM and GMM have the advantages of allowing use of all available data points, which maximizes power to detect effects and reduces bias owing to missing data in longitudinal studies.

The economic evaluation will be a cost-consequences analysis conducted from both the broad societal perspective and the narrower perspective of the health care sector [48]. The economic evaluation will compare any incremental costs of the intervention (costs accrued in the intervention arm compared to costs accrued in the control arm) to the full list of incremental outcomes. The AQoL-8D will allow utility values to be determined (which are used in calculating Quality-Adjusted Life Years (QALYs)) for a cost-utility analysis, which is a more optimal design since QALYs allow comparisons across conditions. The evaluation will include only the costs of intervention delivery (excluding development or research costs), to estimate the resource use required if the multimodal supportive care intervention were rolled-out into practice. Uncertainty in the cost and outcome data and sensitivity of economic evaluation results to the methods of evaluation chosen will be tested through extensive sensitivity analyses. Depending on the results of the evaluation a longer life-time horizon may also be adopted [49].

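### Telephone baseline and mailed follow-up confound each man's change from baseline with a change of mode, which can create or mask the association sought in Hypothesis 3; the randomised comparison is not biased if the shift is common to both arms.

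*Protocol article*

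**What the plan says.** Under Measures, the protocol article fixes the mode by time point. For baseline: "Baseline assessments will be conducted by telephone to facilitate completion of assessments prior to randomisation". For all later visits: "Follow-up assessments will be conducted through written questionnaires that will be mailed to participants". The later visits are "at 3, 6, and 12 months after recruitment and intervention commencement". Study Integrity names both modes ("Assessments will be by telephone and self-report written questionnaires") and contradicts none of this.

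Both primary outcomes are self-reported: unmet needs by the SCNS-SF34 with a prostate module, and activity by the Godin questionnaire ("All men will complete the Godin Leisure-Time Exercise Questionnaire").

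Hypothesis 3, under Study Aims and Hypotheses, reads in part: "For all men, those who show the greatest improvements over time in physical activity will also have the greatest improvements in unmet supportive needs". It extends the same prediction to disease-specific and health-related quality of life.

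Statistical Analyses plans multilevel and growth mixture models with assessments nested in men, and says of them that "they further permit the true assessment of individual change in unmet needs and of the individual predictors of such change (Hypotheses 2 and 3".

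**The concern.** The mode changes once, for every man, between baseline and the first follow-up. No man is assessed in both modes at the same time point, so no later model can separate time from mode at that step. This is fixed by the design that the article states; it is not a detail left to an analysis plan.

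The topics include sexuality needs, distress and exercise, on which answers given by telephone may differ from answers written on paper. Suppose that some men overstate activity and understate need on the telephone. When they move to paper, their recorded activity falls and their recorded need rises. Activity and need then move in opposite directions, which is the pattern that Hypothesis 3 predicts, although nothing has changed in these men. If the shifts were related in the other direction, a real association would be hidden.

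At stake is whether a finding on Hypothesis 3 reflects improvement or response style. Growth curves and mixture classes that start at baseline could likewise partly sort men by how they answer on the telephone.

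**Working it through.** **Inputs from the article.** 250 men per arm are expected to complete, 500 in all. This agrees with the stated recruitment: 500 / 0.85 = 588.2, so 589 against approximately 590. Visits are at 0, 3, 6 and 12 months. The article gives no figure for mode effects, so there is none to reproduce.

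**Assumptions.** Scales have unit variance, with retest correlation 0.6 (independent within-man error variance 0.4). True changes on the two scales are unrelated. Each man has a mode shift of SD s on each scale, with correlation c across scales, both scales being scored so that higher is better. Tests are two-sided at 5%. With n = 500 the critical correlation is tanh(1.96 / √497) = 0.088.

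**Two-point change.** The variance of a change is 2(1 − 0.6) + s² = 0.8 + s², and the covariance between scales is c·s². The spurious correlation is therefore r = c·s² / (0.8 + s²). For c = 0.5 and s = 0.5: 0.125 / 1.05 = 0.119.

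**Linear slope over four visits.** The mean visit time is 5.25 months. The deviations are −5.25, −2.25, 0.75 and 6.75, with sum of squares 78.75. Expressed as 12-month change, the slope gives baseline a weight of 12 × (−5.25) / 78.75 = −0.80, so it carries 80% of the shift. Its error variance is 144 × 0.4 / 78.75 = 0.731. Hence r = c·0.64·s² / (0.731 + 0.64·s²). For c = 0.5 and s = 0.5: 0.080 / 0.891 = 0.090.

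**Results** (rejection rates by Fisher's z, no true association):

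| c | s | r, two-point | False-positive rate | r, four-visit slope | False-positive rate |
|---|---|---|---|---|---|
| 0.2 | 0.2 | 0.010 | 5.5% | 0.007 | 5.3% |
| 0.2 | 0.3 | 0.020 | 7.4% | 0.015 | 6.2% |
| 0.2 | 0.5 | 0.048 | 18.6% | 0.036 | 12.6% |
| 0.5 | 0.2 | 0.024 | 8.3% | 0.017 | 6.6% |
| 0.5 | 0.3 | 0.051 | 20% | 0.037 | 13% |
| 0.5 | 0.5 | 0.119 | 76% | 0.090 | 52% |

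With s = 0 (the same shift for every man) or c = 0 (shifts unrelated across scales), r = 0 and the rate is 5%. Simulation of two-point change with 500 men and 4,000 runs per setting gave 4% to 6% in those cases.

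**Randomised comparison.** A simulation with 250 men per arm, retest correlation 0.7, a mean shift of −0.3 SD and s = 0.5 in both arms gave a between-arm difference of 0.000 and a false-positive rate of 5.6%. Mean change within arms was falsely −0.30 SD.

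**The case against.** The strongest reply is that the main question is untouched and the size is assumed. Both parts stand. A reader might infer that the mode switch biases the trial's primary result. The documents do not support that: both arms change mode at the same point, and a common shift cancels in the comparison.

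A reader might also take the upper rates as an expected error rate. They are not. They need shifts that differ between men and are also correlated across scales, and the article gives neither quantity. The two-point rates also overstate the problem for models that use all four visits, three of which share a mode. A least-squares slope is itself a simplification of the planned models; it shrinks the effect without removing it.

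The article's phrase about true individual change is easily over-read. In context it describes what hierarchical models add by modelling differences between men; it does not claim freedom from mode error. Nor does the article say whether baseline is the first point of the trajectory or a covariate. An interviewer on one side and private completion on the other are inferences from telephone and mail. Self-measured weight, height and waist, and the intervention arm's baseline diary, fit the argument less well than the questionnaires.

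Finally, the telephone has a stated purpose, which is to complete baseline before randomisation, and early change is part of what Hypothesis 3 asks. This weighs against requiring a written baseline or dropping the step from 0 to 3 months. It does not weigh against an additional same-mode analysis.

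**Conclusion.** The concern holds in a limited form. The confounding of mode with the step from baseline to 3 months is certain from the text. Its effect on Hypothesis 3, and on trajectories or classes anchored at baseline, is possible but of unknown size: negligible if shifts are small, uniform or unrelated across scales, and serious at the upper end of the assumed range (shift SD 0.5, cross-scale correlation 0.5). Hypothesis 1 is not biased as long as the shift is common to both arms. The point merits a change because Hypothesis 3 is a stated, non-randomised hypothesis and the safeguard uses data that will be collected anyway.

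**What to change.** Keep the planned analysis. For Hypothesis 3 and the growth and mixture models, pre-specify a companion analysis that uses only the mailed 3, 6 and 12 month assessments, with the telephone baseline as a covariate and not as the first point of the trajectory. Claim support for Hypothesis 3 only if the two analyses agree in direction and rough size. State in the protocol and in the report that change from baseline to 3 months is confounded with mode.

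The cost is a little more analysis and a less precise same-mode estimate that omits early change. For a least-squares slope over 3, 6 and 12 months the visit times have mean 7 and sum of squares 16 + 1 + 25 = 42, against 78.75 for four visits. With independent errors the error variance is therefore 78.75 / 42 = 1.9 times as large. For that reason it should accompany the planned analysis and not replace it.

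Optionally, where it would not delay randomisation, a written baseline sent with the consent pack would remove the problem at source.
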